#### Control intervention

TACE is a well-established alternative to classic chemotherapy in patients with tumors confined to the liver; in this trial, TACE will serve as the control arm. Numerous different TACE techniques have been reported in the literature for treating HCC and CCC
[44, 47, 54]. Since 2006, doxorubicin-loaded DEBs have been commercially available in various sizes. Compared to conventional TACE, which uses Lipiodol mixed with a chemotherapeutic agent, DEBs have been shown to be more effective, with fewer side effects in patients with HCC
[55, 56]. Currently, DEB TACE is the only TACE method that is standardized in terms of the embolization material, the chemotherapeutic agent, and the application technique
[55, 57]. Because we have considerable experience with DcBeads®, we will continue to use them exclusively throughout the trial to ensure reproducibility. The bead size will be 100 to 300 μm.

An optimal dose of 150 mg doxorubicin per application was determined in a prospective trial in patients with HCC
[58]; there will be no dose adjustment made for elevated bilirubin or body surface area. After mixing with nonionic contrast medium, the DcBeads are to be administered slowly, and as selectively as possible with a microcatheter under fluoroscopic control. The mixture will be infused until the flow is sluggish to avoid reflux. In cases of incomplete embolization, additional bland (drug-free) embolization is not permitted. The TACE procedure will be repeated every 6 weeks as this interval has been established in several clinical trials for HCC and intrahepatic CCC
[44, 47, 55, 56, 59]. TACE treatment will be carried out until either no viable tumor tissue is detected by MRI or if any contraindications against repeated treatment occur (for example relevant ascites, portal invasion or occlusion of the arterial feeding vessels). Therefore, additional MRI is indicated prior to each TACE treatment. After cessation of TACE treatment, follow up will be carried on in 3-month intervals until the clinical endpoints are reached. In cases where local tumor progression is detected and no contraindications exist, TACE can be repeated. In cases where contraindications exist, the patient is allowed to cross over to SIRT if there are no contraindications against SIRT.

#### Follow-up

Each follow up will include MRI of the liver, a quality-of-life assessment, documentation of adverse/serious adverse events, a physical examination, and blood tests. All MRI examinations will be performed according to a standardized protocol of MRI sequences, including transversal T1- and T2-weighted images, diffusion-weighted images, and multiphasic contrast-enhanced T1-weighted images. All examinations will be performed on a single 3 T scanner (Skyra®, Siemens Healthcare, Erlangen, Germany).

#### Outcome measures

PFS is directly related to the local treatment result. The local tumor response will be measured with the modified response evaluation criteria in solid tumors (mRECIST) on the basis of the MRI
[60]. In an attempt to eliminate any potential bias that could derive from the difference in follow-up intervals, for determination of PFS only the MRI performed at 3, 6, 9 months et cetera, after the first treatment will be used in both groups (Figure 
1). However, survival is limited by both tumor progression and liver performance. Because both treatments also affect parts of the normal liver parenchyma, they can potentially lead to liver failure. Additionally, extra-hepatic metastases develop more often in patients with intra-hepatic CCC than in patients with HCC. Therefore, PFS will be the primary endpoint, because it includes the local treatment effect, death by deteriorating liver function due to liver toxicity, and death due to extra-hepatic tumor spread.

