### Trial design

#### Experimental intervention

SIRT is a locoregional treatment that selectively irradiates liver tumors. The particles are loaded with the beta emitter Yttrium 90 (Y-90) and are delivered to the hepatic artery or its (sub)-segmental branches in order to embolize and selectively irradiate the tumor. Due to the short range of beta radiation, the tumor is predominantly targeted, and most of the normal liver tissue is spared. The procedure is performed once in each liver lobe. SIRT particles are commercially provided by two companies, and both are acceptable for a prospective study protocol. Based on our significant experience with one of these products, we will use SirSpheres® in this study. The most serious complication associated with SIRT is radiation-induced liver disease, which is, in fact, radiation-induced liver failure; this condition leads to death within a few weeks
[50, 51]. To minimize this complication, the right and left liver lobes will be treated sequentially, with a between-treatment interval of 4 weeks. The liver lobe with the larger tumor mass will be treated first. The dose for each liver lobe will be calculated according to the body surface method
[51, 52]. This is the most frequently used approach for resin spheres (73.5% in a large series of 680 treatments)
[53], and it is recommended by the manufacturer, SIRTEX, and by the Radioembolization Brachytherapy Oncology Consortium (REBOC)
[52].

Patients randomized to SIRT will receive a preparative intervention, including embolization of the collateral arteries (mainly the gastroduodenal artery and the right gastric artery), and subsequently, an MAA scan will be performed. Follow-up visits will be performed at 4 and 12 weeks after completion of SIRT treatment, and every 3 months thereafter until the clinical endpoints are reached. In cases where local tumor progression is detected and no contraindications exist, SIRT can be repeated once in each lobe. In cases where contraindications exist, the patient is allowed to cross over to TACE if there are no contraindications against TACE.

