**Figure 1 Fig1:**
[figure not shown]
**Treatment and follow-up schedule.** Follow up begins after the completion of the first treatment. For determination of progression-free survival (PFS) only the magnetic resonance imaging (MRI) performed at 3, 6, 9 months et cetera, will be used in both groups.

OS is also influenced by drug-induced impaired liver function, by extra-hepatic tumor spread, and by secondary treatment strategies applied after the SIRT/TACE treatment. Therefore, OS is considered a secondary endpoint. Time to progression (TTP) serves as another secondary endpoint. The local tumor response will be determined on the basis of the MRI performed at 3, 6, 9 months et cetera, after the first treatment.

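### The rule fixing which MRIs count for PFS is anchored to the first treatment, but the visit schedules run from completion of SIRT and cessation of TACE, so it does not secure equal reading times in the two arms

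*Protocol article*

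**What the plan says.** Four places in the protocol article govern when a PFS MRI is taken.

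- **Outcome measures.** "for determination of PFS only the MRI performed at 3, 6, 9 months et cetera, after the first treatment will be used", in both groups. The purpose is given in the same sentence: "In an attempt to eliminate any potential bias that could derive from the difference in follow-up intervals".
- **Experimental intervention (SIRT).** "the right and left liver lobes will be treated sequentially, with a between-treatment interval of 4 weeks", and "Follow-up visits will be performed at 4 and 12 weeks after completion of SIRT treatment, and every 3 months thereafter". The anchor is the end of the SIRT course.
- **Control intervention (TACE).** Sessions are repeated every 6 weeks, with an additional MRI before each. Then: "After cessation of TACE treatment, follow up will be carried on in 3-month intervals". The anchor is the end of TACE.
- **Figure 1 legend.** "Follow up begins after the completion of the first treatment". The legend then repeats the 3, 6, 9 month rule for both groups.

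The Follow-up section ties imaging to these visits: "Each follow up will include MRI of the liver, a quality-of-life assessment, documentation of adverse/serious adverse events". The Abstract mentions MRI every 3 months without an anchor. No section states the time origin of PFS, TTP or OS; only the MRI times are tied to the first treatment.

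**The concern.** Progression is seen only when a scan is read, so the scan calendar becomes part of the PFS estimate. The authors recognised this and wrote a rule to neutralise it. The rule works only if both arms are scanned at the times it names, and the arm-specific schedules, taken as written, are counted from different events.

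The Statistical analysis section makes estimates of PFS, OS and TTP the main purpose, by Kaplan-Meier methods. The Discussion would use the results to size a confirmatory trial. With 12 patients per arm, a difference produced by the calendar could be carried forward as a treatment difference.

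**Working it through.** **Inputs.** From the article: targets at 3, 6, 9 months after the first treatment; SIRT lobes 4 weeks apart; SIRT visits 4 and 12 weeks after completion, then 3-monthly; TACE sessions and pre-session MRIs every 6 weeks; 3-monthly follow-up after TACE stops. Conversion: 1 month = 365.25/12/7 = 4.348 weeks, so 3 months = 13.04 weeks. Week 0 is the first administration.

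**Targets.** 13.04k weeks: 13.0, 26.1, 39.1, 52.2.

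**SIRT, two lobes.** Completion is at week 4. MRIs are at 4+4 = 8 and 4+12 = 16, then 16+13.04 = 29.0, 42.1, 55.1. The nearest MRI is 3.0 weeks after every target.

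**SIRT, with first treatment read as the completed course (or one lobe only).** MRIs are at weeks 4, 12, 25.0, 38.1, 51.1 on that clock, 1.0 week before every target. For a two-lobe course the scans have not moved; the clock now starts at least 4 weeks after first administration. The same reading applied to TACE would start its clock at cessation, week 6(n−1) after n sessions, which differs by patient.

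**TACE, on treatment.** MRIs are at weeks 6, 12, 18, 24, 30, 36, 42. The nearest to the targets are week 12 (−1.0), week 24 (−2.1) and week 42 (+2.9; week 36 is −3.1).

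**TACE, after n sessions, follow-up counted from the last one.** MRIs are at 6(n−1) + 13.04k weeks:

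| Sessions | Offset from target after cessation (weeks) |
|---|---|
| 1 | 0.0 |
| 2 | +6.0 |
| 3 | −1.0 |
| 4 | +5.0 |
| 5 | −2.1 |
| 6 | +3.9 |
| 7 | −3.1 |

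Counting from the MRI that ended treatment shifts this pattern by one session.

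**Effect on the mean.** Assume the same exponential progression time in both arms, with rate λ = ln 2 / median and S(t) = exp(−λt), read at the next counted MRI. For a first read at week a and then every d weeks, the mean read time is a + d·S(a)/(1 − S(d)). SIRT has a = 16 and d = 13.04. TACE is taken as read every 12 weeks (a = d = 12).

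- Median 3 months (λ = 0.0531 per week). SIRT: 16 + 13.04 × 0.427/0.500 = 27.1 weeks = 6.24 months. TACE: 12/(1 − 0.529) = 25.5 weeks = 5.85 months. Difference 0.39.
- Median 6 months: 10.38 v 10.11. Difference 0.27.
- Median 12 months: 18.92 v 18.73. Difference 0.2.

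The size and sign depend on the TACE pattern. If every TACE patient stopped after 2 sessions (a = 19.04, d = 13.04), the TACE mean at a true median of 3 months is 19.04 + 13.04 × 0.364/0.500 = 28.5 weeks = 6.56 months, which is 0.32 months later than SIRT.

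**Effect on the median.** The read median is the first counted MRI at or after the true median.

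| True median (months) | SIRT read (weeks) | TACE read, 12-weekly (weeks) | SIRT minus TACE (months) |
|---|---|---|---|
| 3 | 16 | 24 | −1.8 |
| 4 or 5 | 29 | 24 | +1.2 |
| 6 | 29 | 36 | −1.6 |
| 8 | 42 | 36 | +1.4 |
| 10 | 55 | 48 | +1.6 |
| 12 | 55 | 60 | −1.1 |

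**The case against.** The best defence is that the text allows a reading on which the arms nearly agree. SIRT may be repeated and the Figure 1 legend speaks of completing the first treatment, so first treatment may mean the first SIRT course; its 12-week visit is then the 3-month MRI, one week early. The pre-session TACE MRIs are called additional, so they may come on top of a 3-monthly series already running, and follow-up being carried on after TACE may mean continued rather than restarted. Figure 1 itself is not available, and visit windows may be in the full protocol. Finally, this is an exploratory pilot with no confirmatory test to invalidate.

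Much of this stands as a limit on the point:

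- A reader might infer that neither arm's schedule ever produces the required MRIs. That is too strong. On-treatment TACE scans come within 1 to 2 weeks at months 3 and 6, and TACE stopped after one session can match exactly.
- A reader might infer that time zero is the first treatment, so that deaths during the SIRT work-up are lost. The article does not say so; it states no origin for PFS, TTP or OS. Such a loss would occur only if treatment were the origin.
- A reader might infer that quality of life and adverse events in the TACE arm are recorded only after the whole course. The Figure 1 legend, which starts follow-up after the first treatment without distinguishing arms, does not support that.
- A reader might take the differences in read medians as a bias towards one arm. Their sign changes with the assumed true median, so they are an artefact of the visit grid.

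The favourable reading does not remove the inconsistency. It brings SIRT near its targets only by starting the SIRT clock at least 4 weeks after first administration, and it needs a different meaning of first treatment for TACE. The exploratory label does not help either, because the estimates themselves are the product.

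**Conclusion.** The sections use different anchors for the MRIs that decide the primary endpoint, and no single literal reading keeps both arms on the stated calendar throughout. A rule written to remove assessment-time bias therefore does not do so. The calendar offsets follow from the article's own intervals. The effect on PFS is modest on average: 0.2 to 0.4 months under equal exponential PFS with assumed medians of 3 to 12 months, two-lobe SIRT and 12-weekly TACE reads, and smaller or reversed for some TACE session counts. Read medians are less stable, differing by up to about 1.8 months with either arm ahead. This weakens the estimates; it does not predict which arm will look better.

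**What to change.** Reconcile Experimental intervention, Control intervention, Outcome measures and the Figure 1 legend so that they describe one endpoint calendar: MRI at 3, 6, 9 months and so on from randomisation, with the same stated window in both arms, independent of treatment sessions. Count PFS, TTP and OS from randomisation and say so. This matters because only the SIRT arm has a preparative intervention and MAA scan between randomisation and treatment, of unstated duration. MRIs done to guide treatment stay as they are for care.

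The cost is an amendment of the visit wording and moving some endpoint MRIs by a few weeks. Reported PFS will include the gap from randomisation to first treatment, which should be noted when it is compared with series that count from treatment.

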**Figure 1 Fig1:**
[figure not shown]
**Treatment and follow-up schedule.** Follow up begins after the completion of the first treatment. For determination of progression-free survival (PFS) only the magnetic resonance imaging (MRI) performed at 3, 6, 9 months et cetera, will be used in both groups.

OS is also influenced by drug-induced impaired liver function, by extra-hepatic tumor spread, and by secondary treatment strategies applied after the SIRT/TACE treatment. Therefore, OS is considered a secondary endpoint. Time to progression (TTP) serves as another secondary endpoint. The local tumor response will be determined on the basis of the MRI performed at 3, 6, 9 months et cetera, after the first treatment.

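### Follow-up and the PFS scans are timed from an undefined first treatment instead of randomisation, so the two arms can start their clocks at different times and untreated patients have no start date

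*Protocol article*

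**What the plan says.** Four places in the Protocol article set a clock, and they do not use the same event.

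- **Outcome measures:** for PFS, "only the MRI performed at 3, 6, 9 months et cetera, after the first treatment will be used in both groups". The stated reason is "In an attempt to eliminate any potential bias that could derive from the difference in follow-up intervals".
- **Figure 1 caption and the text below it:** "Follow up begins after the completion of the first treatment", and "The local tumor response will be determined on the basis of the MRI performed at 3, 6, 9 months et cetera, after the first treatment". The same scan timing is repeated in the section headed Determination of primary and secondary measures.
- **Experimental intervention:** "Patients randomized to SIRT will receive a preparative intervention, including embolization of the collateral arteries", followed by an MAA scan. Then "the right and left liver lobes will be treated sequentially, with a between-treatment interval of 4 weeks". Visits are counted from the end of the course: "Follow-up visits will be performed at 4 and 12 weeks after completion of SIRT treatment, and every 3 months thereafter".
- **Control intervention:** TACE is repeated every 6 weeks, and 3-monthly follow-up starts when TACE stops. No separate preparative procedure is described.

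First treatment is not defined as one session or one course. Time zero for PFS, OS or TTP is not stated anywhere, and none of these sections mentions randomisation as the starting point.

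**The concern.** A randomised comparison is protected only if both groups are followed from the same moment, and randomisation is the one moment they share. Here the stated anchor is an event after randomisation, and the route to it differs by arm. SIRT patients must first pass through preparation and the MAA scan; no such step is described for TACE.

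Three things are at stake.

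1. The common scan grid is meant to remove interval bias. It cannot do that fully if the grid hangs on an event that the two arms reach at different times.
2. A patient who is randomised but never treated has no anchor. The article makes this possible: a hepatopulmonary shunt of 20% or more on the MAA scan is an exclusion criterion, yet the scan is described for patients already randomised to SIRT. Under Participants, recruitment then continues after dropouts until the smaller group has 12. Patients lost before SIRT could therefore be replaced by patients who reached it.
3. PFS was chosen partly because it captures death from liver toxicity. The article describes the most serious SIRT complication as "radiation-induced liver failure; this condition leads to death within a few weeks". On one reading of the anchor, part of that risk period lies before follow-up begins.

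Statistical analysis calls the estimates of PFS, OS and TTP the main purpose, and the Discussion would use the results to size a confirmatory trial.

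**Working it through.** The article gives no power, event or effect figure to reproduce; 12 + 12 = 24 is consistent.

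**Step 1. When each arm reaches the anchor.** Let p be the SIRT preparation time in weeks (not stated). Take the TACE wait as zero for simplicity, although TACE patients also wait somewhat. The article gives 4 weeks between lobes, 6 weeks between TACE sessions, and 4 to 10 TACE treatments (The need for a trial, in its comparison with SIRT for HCC).

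| Meaning of the anchor | SIRT | TACE | Later arm |
|---|---|---|---|
| One session in each arm | p | 0 | SIRT, by p |
| Both lobes for SIRT, one session for TACE | p + 4 | 0 | SIRT, by p + 4 |
| Full course in each arm | p + 4 | (4−1)×6 = 18 to (10−1)×6 = 54 | TACE, by 14−p to 50−p |

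**Step 2. Which reading fits the visit schedule.** Three months is 3 × 52.18/12 = 13.0 weeks. The SIRT visits fall 4 + 4 = 8 and 4 + 12 = 16 weeks after the first lobe. If the anchor is the first lobe, the 3-month PFS scan matches neither visit. If it is completion of both lobes, the 12-week visit lies close to it. The text does not settle the matter.

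**Step 3. Size if time zero is the start of follow-up.** With exponential PFS, the share of events before the clock is 1 − exp(−ln 2 × delay/median). For a 4-week delay and a 6-month median (26.1 weeks): 1 − exp(−0.693 × 4/26.1) = 0.101, and 0.101 × 12 = 1.2 patients. The medians and the 8-week delay are assumptions.

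| Median PFS (months) | 4-week delay | 8-week delay |
|---|---|---|
| 3 | 19% (2.3 of 12) | 35% (4.2 of 12) |
| 6 | 10% (1.2 of 12) | 19% (2.3 of 12) |
| 9 | 7% (0.8 of 12) | 13% (1.6 of 12) |
| 12 | 5% (0.6 of 12) | 10% (1.2 of 12) |

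One patient in 12 is 100/12 = 8.3 points on the curve. These shares are not all lost events: a patient who progresses in the window and survives is still scanned, and only the origin shifts.

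**Step 4. Size if events are dated from randomisation.** One million patients per arm were simulated with equal hazards. Scans ran every 3 months from each arm's anchor, and each event was recorded at the next scan. The apparent SIRT/TACE rate ratio is mean recorded time on TACE divided by that on SIRT. At a 6-month median and 4-week delay it is 10.23/10.43 = 0.98.

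| Median PFS (months) | 4-week delay | 8-week delay |
|---|---|---|
| 3 | 0.94 | 0.88 |
| 6 | 0.98 | 0.96 |
| 9 | 0.99 | 0.98 |

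Recorded medians are unstable here because the assumed medians fall on TACE scan dates. With a 4-week delay, TACE against SIRT was 6.0 against 6.9 months at the 6-month median, and 12.0 against 9.9 at 9 months.

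**Step 5. With randomisation as the anchor** and scans at 3, 6, 9 months from it in both arms, the offset is zero, no event precedes the clock, and N stays 24.

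**The case against.** The strongest defence has four parts.

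- **The article tends to count sessions.** It calls the gap between lobes a between-treatment interval, and the word completion of the first treatment stands only in a caption whose figure is not available here. On a session reading the 4 weeks disappear and a death after the first lobe falls inside follow-up. This stands as an argument, but Step 2 shows the SIRT visit schedule fits the other reading better. The ambiguity remains, and so does the preparation offset.
- **Time zero is commonly left to the analysis plan.** True, and its absence alone would not be a finding. The difficulty is that the article does fix a start of follow-up and a scan clock, and both are treatment-based.
- **Timing scans from treatment is defensible for a local therapy.** This stands for response assessment. It does not help the comparison of PFS between arms.
- **The trial is exploratory and unpowered.** This stands and limits the severity: no confirmatory error rate is at risk.

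A reader might infer that every reading favours SIRT. The documents do not support that, because full courses in both arms would make TACE the later arm. A reader might also infer that deaths after the first lobe are excluded. No passage excludes early deaths, and Outcome measures names toxicity deaths as part of PFS. Losing them needs two further steps: a course reading for SIRT only, and time zero at the start of follow-up. Finally, one could apply the 27.6% one-year survival under Prognosis to an assumed 5 to 6 week window and obtain 12 to 14% deaths. That figure is for intrahepatic disease in 1995 to 1999, and is not a fair central case for patients selected for ECOG 0 to 1, liver-confined tumour and preserved liver function.

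**Conclusion.** The point holds in a limited form. The start of follow-up and the PFS scan clock are tied to an undefined, treatment-based event that the arms reach at different times, and patients never treated have no start date. This works against the article's own aim of removing interval bias.

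Neither the direction nor the size is settled. Counting sessions, SIRT is later by an unstated preparation time. On the mixed reading it is later by 4 weeks more, and a toxic death after the first lobe could precede follow-up. Counting courses, TACE is later. For a 4-week offset and an assumed 6-month median PFS, the consequence ranges from about 1.2 of 12 SIRT patients with a PFS event before the clock down to an apparent rate ratio of about 0.98, depending on time zero. It is larger if PFS is short or preparation is long. For an exploratory pilot this is a moderate correction, worthwhile because the estimates are the trial's main product.

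**What to change.** 1. State that PFS, OS and TTP run from the date of randomisation for every randomised patient, treated or not, and that deaths and other events are recorded from that date.
2. Date the MRIs that determine PFS at 3, 6, 9 months from randomisation in both arms.
3. Wherever the term first treatment is kept, define it identically for SIRT and TACE. Reconcile Experimental intervention, Control intervention, Outcome measures, the Figure 1 caption and Determination of primary and secondary measures.

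**Cost.** This is wording in the protocol and analysis plan; the randomisation date is already known and the sample size does not change. The SIRT estimates may become slightly less favourable. The first PFS scan also falls sooner after SIRT: with an assumed 1 to 2 weeks of preparation, 13 − 4 − (1 to 2) = 7 to 8 weeks after the second lobe. That should be weighed when the scan dates are aligned with the SIRT visits.
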